#### Psychosocial Screening

In addition to risk adjustment, a formal assessment of levels of psychological distress and / or depression of patients will be made due to the fact that it is now widely accepted that such factors are strong predictors of outcome in musculoskeletal conditions (Main et al., 2007) and that pain is best viewed as a multi-dimensional phenomenon, comprising biological, psychological, social and existential elements (Westman et al., 2008). For the individual patient, persistent musculoskeletal pain has been shown to significantly affect the patient's quality of life with symptoms usually being continuous and disrupting a variety of functions (Costa Lda et al., 2011, Heymans et al., 2010, Lin et al., 2011). However, it must be remembered that not all

patients develop chronic problems – for example it has been shown that after an acute bout of back pain, only a small percentage (3–10%) of patients developed long-term work absence but this small number consumed approximately 75–85% of the available resources (Reid et al., 1997, Nachemson et al., 2000, Friedly et al., 2010). The Örebro Musculoskeletal Pain Questionnaire (ÖMPQ) will be used for this formal assessment on the basis of its predictive ability to identify patients who will have a poor outcome across a range of musculo-skeletal conditions – acute, subacute or chronic, and different body regions; any improvements (or lack of improvements) in the other outcome measures need to be cross-referenced with these profiles. (Brown, 2008, Dunstan et al., 2005, Gabel et al., 2010, Hockings et al., 2008, Johnston, 2009, Linton and Boersma, 2003, Maher and Grotle, 2009, Margison and French, 2007, Westman et al., 2008).

### Analysis

The ÖMPQ will be scored and interpreted at the start of treatment as per the scoring instructions:

- For question 1, count the number of pain sites and multiply by two – this is the score (maximum score allowable is 10).
- For questions 2 and 3 the score is the number bracketed after the ticked box.
- For questions 4, 5, 6, 7, 9, 10, 11, 14, 15 and 16 the score is the number that has been circled.
- For questions 8, 12, 13, 17, 18, 19, 20 and 21 the score is 10 minus the number that has been circled.

A total score of 105 or above indicates persons who are at risk of disability or failure to return to work.

### Therapist Outcome Measures

Therapist performance will be assessed by an independent assessor, using the criteria currently used by tutors at the University of Birmingham to assess improvements in performance of physiotherapists as part of the summative assessment of the Evidence Based Clinical Practice module of their MSc in Advancing Practice and Advanced Manipulative Physiotherapy programmes (see Appendix D). This will take place at all 3 data collection points (baseline and post each intervention). As these courses - and this module - has been approved by the MACP and its international umbrella organization IFOMPT, the use of an agreed set of marking criteria that distinguishes advanced practice in manipulative physiotherapy for the outcome of the practice based experience, is required for continued accreditation by the MACP. The module's marking criteria, therefore, contain these agreed criteria. On a practical level, accreditation specifies that the summative assessment encompasses the evaluation of a minimum of one new and one follow-up patient (IFOMPT, 2008). This study will utilize the same basis for assessment of therapist performance, where the therapist will be observed by an independent (non-health board employee), experienced (familiar with - and experienced in - using the University of Birmingham criteria) assessor who will observe the therapist with a new patient and follow up patient.

In addition to being informed by nationally applied international standards of educational practice, the University of Birmingham criteria (in preference to other University course criteria) are supported by empirical data (Rushton and Lindsay, 2010, Rushton and Lindsay, 2008). One study (Rushton and Lindsay, 2008) explored Masters courses in the United Kingdom assessing clinical practice (nursing/midwifery, physiotherapy, radiography, and inter-professional) using a modified Delphi-technique to define the behaviours indicative of the construct of masters level clinical practice. There was a very good response rate by the course tutors for the Delphi study (79.1%) and the level of consensus for the behaviours identified for the first round was good (with the three most commonly occurring behaviours being provided by more than 60% of the participants, and a further five behaviours provided by more than 50%). The second round required ranking of the importance of each behaviour identified from themes from first round data by the

participants; again there were high levels of agreement from participants for the importance of most behaviours (indicated by high mean scores and low standard deviations and values of the coefficient of variation). The third round required participants to rank the importance of the different behaviours to Masters level clinical practice. Incidentally, but significantly for this research, consensus across all participants identified a high level of clinical reasoning as having the greatest importance to the construct. There was statistically significant agreement across all participants and within both the physiotherapy group and the radiography group, but rankings differed between professions and participants reported that they would rank differently according to speciality within a profession. The lowest ranked behaviour was removed due to the low level of consensus. The resulting 20 behaviours demonstrated good measurement validity and external validity. It is these behaviours from this study that have produced the construct for the marking criteria in use for the University of Birmingham's Masters Courses seeking to develop clinical expertise.

The same authors (Rushton and Lindsay, 2010) also explored the construct of masters level manipulative physiotherapy clinical practice in its real life context, using an exploratory case study of the University of Birmingham Masters course in Manipulative Therapy. Semi-structured interviews with thirteen students and eleven clinical tutors formed part of the research, and implicit use of the construct were explored by participant observation of seven clinical examinations. Triangulation of data across methods, and convergence with the Delphi study discussed previously (Rushton and Lindsay, 2008) informed the conclusions. Again, the most important behaviour associated with the construct for manipulative physiotherapy was identified as a high level of clinical reasoning and validation of the construct was supported by convergence of data with the Delphi study.

In other studies exploring the effect of educational interventions using crossover methodology, (Cook et al., 2007, Murray et al., 1997a) the point is made that assessment needs to be appropriate – specifically comparisons of students using pre and post intervention testing, a design which has been widely accepted and favoured as a method of assessing the efficacy of skills teaching. While the primary outcome measure for this study - patient outcome measurement - appears to be a new venture for educational interventions, the undertaking of pre-and post-exposure assessment using a widely accepted and nationally and internationally recognized method for assessment of clinical performance satisfies this demand.

All of this serves to underpin the assessment of physiotherapist performance in this study by utilising the University of Birmingham construct for the assessment of improvements in performance of physiotherapists, by observing each therapist with one new patient and one returning patient at three data collection points. Assessment of participants at step 1 will give baseline data on performance levels; assessment of participants during step 2 or 3 will ensure that the independent assessor will not know if therapists have received training or not; assessment during step 4 will give post-intervention measures for all participants.

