## Methods - Interventions

### Intervention

The first step (time point) corresponds to a baseline measurement where none of the clusters receive the intervention, which is usual practice for this design (Hussey and Hughes, 2007). At each subsequent step a cluster of participating physiotherapists (a department of the MSK outpatient physiotherapy service) will cross over from control to receive the intervention - a 150 hour clinical mentorship programme, aimed at facilitating clinical reasoning. This will be delivered to participating physiotherapists by mentors who are MACP members, having qualified at MSc / PgD level from a higher education establishment, and who have experience in delivering this form of mentorship at post-graduate level. The intervention will be delivered at the start of the time period, to allow for consolidation and application of the programme, before data collection occurs at the end of the time period. This intervention is selected on the basis that the use of mentorship in the context of clinical placement is established practice in Master's programmes seeking to develop expert practice and has strong support from qualitative literature as outlined earlier. The intervention will take place in the usual clinical context of the participating physiotherapists (as is current practice), consisting of the mentors observing the participating physiotherapists assessing and treating new and follow-up patients, discussing and facilitating clinical reasoning processes immediately after the patients have left. While this programme needs to be fluid enough to address identified learning needs and errors in clinical reasoning, a framework on which to hang discussion, feedback and reflection sessions will help to standardize the intervention to a point; the dialectical clinical reasoning model of Jones and Edwards, 2007 (see figure 4 below) will be implemented to this end. This model has been selected due to its flexibility for management and assessment paradigms, its adaptability to patient situations and presentations, and its underpinning research (Edwards et al., 2004, Edwards et al., 2006, Edwards and Jones, 2007). Failure of participants to receive the intervention will be reported, as well as the reasons for such failure.

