### Hypotheses

H: There will be a significant difference in the risk-adjusted outcomes of patients whose physiotherapists have received training in clinical reasoning skills via a clinical mentoring programme when compared with those whose physiotherapists have received standard training.

H: There will be no difference in the risk-adjusted outcomes of patients whose physiotherapists have received training in clinical reasoning skills via a clinical mentoring programme and those whose physiotherapists have received standard training.

H: There will be a significant improvement in the performance of physiotherapists who have received training in clinical reasoning skills via a clinical mentoring programme when compared with their performance having received standard training.

H: There will be no improvement in the performance of physiotherapists who have received training in clinical reasoning skills via a clinical mentoring programme when compared with their performance having received standard training.

H: There will be a correlation between improvements in the performance of physiotherapists who have received training in clinical reasoning skills via a clinical mentoring programme and improvements in the clinical outcomes of their patients.

H: There will be no correlation between improvements in the performance of physiotherapists who have received training in clinical reasoning skills via a clinical mentoring programme and improvements in the clinical outcomes of their patients.

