#### Randomisation

The stepped wedge design is a one-way crossover design in which different clusters cross over (switch treatments) at different time points (Mdege et al., 2011). In addition, the clusters cross over in one direction only—typically, from control to intervention. The first time point usually corresponds to a baseline measurement where none of the clusters receive the intervention of interest. At subsequent time points, clusters initiate the intervention of interest and the response to the intervention is measured. More than one cluster may start the intervention at a time point, but the time at which a cluster begins the intervention is randomized (Brown and Lilford, 2006, Hussey and Hughes, 2007).

Enrollment: participating physiotherapists will be recruited by the lead researcher by invitation on the basis of inclusion criteria. They will be approached by the lead researcher, and issued with participant information sheet version 2.0 (see appendix C). The lead researcher will also obtain written consent with participant consent form version 2.0 (see appendix C). During data collection periods, patients will be recruited by their physiotherapist, and issued with patient information sheet version 1.0 (see appendix B). The physiotherapist will also obtain written consent with patient consent form version 1.0 (see appendix B).

Sequence generation: once consented by the lead researcher, participating therapists will be directed to the clinical mentors. The clinical mentors will then randomly allocate the clusters of physiotherapists (clustering by site) to the sequence of intervention (to receive the intervention in time period 2, 3 or 4), by computer programme (Randomization.com, 2008).

Allocation concealment: The sequence generation will be performed by the allocated mentor, in order to ensure that this sequence allocation will be adequately concealed from the lead researcher, who will remain blinded to the sequence until after the data collection and analysis period is completed. These measures for blinding, sequence generation and allocation concealment are implemented to reduce the risk of bias, as highlighted by the Cochrane risk of bias tool (Armijo-Olivo et al., 2010, Lundh and Gotzsche, 2008).

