### **Blinding (Masking)**

As with all other evaluations, masking patients, caregivers and observers, as well as those undertaking the statistical analysis is important in minimising information bias (Schulz et al., 2002, Schulz and Grimes, 2002). Due to the fact that in stepped wedge trials the timing of intervention rollout is the unit of randomization, the participating physiotherapists and intervention implementers (clinical mentors) are aware of which cluster is receiving the intervention (Brown et al., 2008, Mdege et al., 2011). However, it is possible to blind the outcome assessors, in this case the lead researcher (who will be unaware of the sequence allocation when analysing outcome data) and the independent observer of physiotherapist performance. This blinding of outcome assessors and use of sequence generation and allocation concealment is essential to enhance internal validity (Brown et al., 2008). Patients submitting their outcomes will also be unaware of whether or not their allocated physiotherapist has received his/her intervention.

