Another challenge is the possibility that the full effect of the intervention may not be realized until several time intervals following implementation, for example, the intervention being 50% effective after the first time interval, 75% effective after the second time interval and 100% effective after the third time interval (Hussey and Hughes, 2007). Delayed effects from the intensive mentoring for clinical reasoning facilitation are possible, with physiotherapists requiring time to consolidate and make practice changes. The overall effect of these delayed effects would be to reduce power. Such delays can be modelled into the power calculations, and power can be recovered in part by adding additional measurement periods to the end of the trial. However, it is preferable to address this issue by making the time intervals sufficiently long to see the effects of the intervention realized in a single interval (Hughes, 2007, Hussey and Hughes, 2007). To address this, the clinicians who will act as clinical mentors in this study were asked to reflect on their own experience following mentoring programmes from their Masters courses, and estimate what time period they thought would be sufficient to consolidate knowledge and change practice. All responses estimated between 6-12 months. To this end, each time period will be 12 months long, with the intervention delivered at the beginning of the time period and the data collection at the end of the period to allow for the full effects of the intervention to make an impact.

One group of authors (Brown et al., 2008) highlight the amount of data collection required as the main disadvantage of the stepped wedge design, which could make the cost of using the design prohibitive, unless

the study can use routine, or other easily collected data. This study aims to collect patient outcome data at first and final appointments which is part of routine practice in the physiotherapy service at the Cardiff and Vale University Health Board. An additional collection of these outcomes will take place 12 months post discharge by telephone. Demographic and cost-effectiveness data will be collected at the same time in a single compiled questionnaire. This would certainly fit the description of routine, easily collected data.

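### Therapist performance: the step 1 to step 4 change cannot be separated from about 36 months of calendar time, and the one comparative visit is left loosely at step 2 or 3

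*Protocol*

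**What the plan says.** The second hypothesis in the protocol (Hypotheses) is that therapists improve after mentoring "when compared with their performance having received standard training". The third hypothesis correlates that improvement with patient outcomes. An independent assessor from outside the health board marks performance.

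Therapist Outcome Measures describes the visits twice. Its opening paragraph says: "This will take place at all 3 data collection points (baseline and post each intervention". Its closing paragraph makes step 1 the baseline, then states that "assessment of participants during step 2 or 3 will ensure that the independent assessor will not know if therapists have received training or not", and that "assessment during step 4 will give post-intervention measures for all participants".

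The roll-out is set elsewhere. The first step "corresponds to a baseline measurement where none of the clusters receive the intervention" (Intervention). Clusters are randomised "to receive the intervention in time period 2, 3 or 4" (Randomisation). Finally, "each time period will be 12 months long, with the intervention delivered at the beginning of the time period" (Challenges in using this design and how they will be addressed).

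Blinding (Masking) names the lead researcher "and the independent observer of physiotherapist performance" as outcome assessors who can be blinded. It does not restrict this to particular visits.

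**The concern.** Labelling step 1 as baseline and step 4 as post-intervention invites a before-after reading of the performance hypothesis. In this design those are exactly the two visits at which training status does not vary between therapists. Ordinary professional growth, usual training (which includes monthly mentoring) and drift in the assessor's marking would all be credited to the programme. The correlation hypothesis would inherit the same change score.

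The middle visit is the only one that can separate training from time, and it is the one whose timing is not fixed. A reader who takes the blinding section at face value would also trust the step 1 and step 4 marks more than the protocol's own reasoning supports.

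**Working it through.** **Inputs.** 12 therapists in 3 clusters (Eligibility criteria for participant clusters), four per cluster (Table 5). Crossovers fall in periods 2, 3 and 4, and each period lasts 12 months. The protocol gives no SD, between-visit correlation or target difference for performance. Results below are therefore in SD units of a performance mark, for an assumed correlation ρ between any two visits by the same therapist.

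**Step 1: confirm the roll-out pattern from the protocol's own figure.** Trained therapists by step:

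| Cluster | Step 1 | Step 2 | Step 3 | Step 4 |
|---|---|---|---|---|
| First to cross | 0 | 4 | 4 | 4 |
| Second to cross | 0 | 0 | 4 | 4 |
| Third to cross | 0 | 0 | 0 | 4 |
| **Total of 12** | **0** | **4** | **8** | **12** |

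- U = 0+4+8+12 = 24
- W = 0+16+64+144 = 224
- V = 4×(9+4+1) = 56

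These are the Appendix E values. With σ² = 4/9 and τ² = 1, the Hussey and Hughes variance is

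Iσ²(σ²+Tτ²) / [(IU−W)σ² + (U²+ITU−TW−IV)τ²] = (5.333×4.444)/(28.444+160) = 0.125786.

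This gives Δ = 1/√0.125786 = 2.8196 and power 0.805, as stated. That calculation is for the PSFS. It is used here only to confirm the 0, 4, 8, 12 pattern.

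**Step 2: steps 1 and 4 alone.** Take mark = mean + step effect + θ × trained + therapist effect + error. With visits only at steps 1 and 4, the training indicator equals the step 4 indicator. The fixed-effects matrix has rank 2 for 3 parameters, so θ is not estimable. Without step effects, all of 3×12 = 36 months of change is counted as training effect: a gain of g marks a year adds 3g. For illustration only, assumed gains of 1, 2 and 3 marks a year would add 3, 6 and 9 marks. Most passing grade bands in Appendix D are 10 marks wide.

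**Step 3: schedules that the step 2 or 3 wording allows**, with visits at steps 1 and 4 for everyone and step effects in the model:

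| Middle visit | Rank / parameters | SE of θ (SD), ρ=0.3 | ρ=0.5 | ρ=0.7 |
|---|---|---|---|---|
| All at step 2, or all at step 3 | 4/4 | 0.568 | 0.500 | 0.399 |
| Each cluster split evenly between steps 2 and 3 | 5/5 | 0.568 | 0.500 | 0.399 |
| First cluster at step 2, other two at step 3 | 5/5 | 0.656 | 0.577 | 0.460 |
| First cluster at step 3, other two at step 2 | 4/5 | not estimable | not estimable | not estimable |
| First two clusters at step 3, third at step 2 | 4/5 | not estimable | not estimable | not estimable |

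In the last two rows everyone seen at step 2 is untrained and everyone seen at step 3 is trained, so status again coincides with step.

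The first row can be checked by hand: SE² = (1/4+1/8)×[1−2ρ²/(1+ρ)]. At ρ = 0.5 this is 0.375×0.6667 = 0.25, so SE = 0.500. Approximate 95% half-widths run from 1.96×0.399 = 0.78 SD to 1.96×0.568 = 1.11 SD.

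**The case against.** **No before-after test is prescribed.** A reader might infer that the protocol plans a paired step 4 minus step 1 test. It does not say so. Statistical methods bases the analysis on stepped-wedge procedures with a random intercept, the Challenges section adds time effects, and a statistical analysis plan may give the detail. This stands. Step effects do not rescue the step 1 to step 4 contrast, however; they make it non-estimable. Statistical methods also permits a within-cluster analysis if no temporal effects are found. The visit schedule itself is set in the protocol.

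**Unblinded is too strong.** A reader might infer that the assessor is unblinded at steps 1 and 4. Nothing says the assessor is told the step or the roll-out scheme. All therapists share one status at each of those visits, so expectation could shift a whole visit but could not favour trained over untrained therapists within it. What stands is narrower: status can be inferred by anyone who knows the step, no measure to hide the step is described, and the protocol itself credits masking to the middle visit alone.

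**The number of assessments does not conflict.** A reader might count baseline plus three crossovers as four. Elsewhere the protocol uses the word interventions for both conditions, mentoring and usual training, and both descriptions say three visits. The remaining problem is that a single middle visit does not follow the same condition in every cluster.

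**Step 2 or 3 may mean one collective visit.** That reading is possible and harmless. Estimability is lost only under particular allocations, none of them prescribed. The failing ones do follow training status, so they could arise if visits are timed to a therapist's condition.

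**Precision is not the fault.** The SE of the before-after change (0.289 SD at ρ = 0.5) is smaller than 0.500, and a reader might conclude that precision is overstated. These are different estimators. The smaller SE is correct for the change itself; the problem is bias.

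**Conclusion.** The point holds in a limited form. The step 1 to step 4 change in performance is completely confounded with about 36 months of time and cannot by itself show an effect of mentoring. The interval is approximate, because assessments are placed during a step and not on a date. Identification rests on the middle visit, whose wording permits both sound schedules and schedules under which the step-adjusted effect cannot be estimated. The blinding section claims more than Therapist Outcome Measures supports.

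With one common middle step the SE is about 0.40 to 0.57 SD for an assumed ρ of 0.7 to 0.3. This is optimistic. It treats 12 therapists as independent, whereas the concurrent contrast sets one randomised cluster against two, and any variation shared within a cluster and period would widen it. The drift in marks per year is an assumption, not a figure from the protocol.

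Two of the three hypothesis pairs depend on this score. It is not the primary outcome, its objective is worded as exploratory, and the PSFS analysis is not directly affected. It should be corrected, but it does not undermine the trial.

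**What to change.** 1. Set the middle assessment in advance at one common step for all therapists, either all at step 2 or all at step 3. Under the assumptions above the precision is the same.
2. Test the performance hypothesis with step effects and a therapist random intercept, in line with Statistical methods and the Challenges section, keeping the step effects whether or not they appear significant.
3. Report the step 1 to step 4 change alone as descriptive, including where it feeds the correlation with patient outcomes.
4. In Blinding (Masking), limit the statement about the performance observer to the middle visit, or say how the step is hidden from the assessor.
5. Align the opening paragraph of Therapist Outcome Measures with its closing paragraph on when the three assessments occur.

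The cost is scheduling and wording, with no extra assessments. The price is a wider interval that rests on one randomised cluster against two. If that is judged too imprecise, assessing everyone at all four steps would need 12 further assessments and would lower the SE at ρ = 0.5 from 0.50 to 0.37 SD, with the same caveat about independence.
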